### Intervention description {11a}

Patients randomized to group 1 will receive standard-of-care treatment for patients with aSAH according to the European guidelines [18]. Continuous ICP monitoring will be performed throughout aSAH treatment in order to detect pathological increases of ICP.

Patients randomized to group 2 will receive standard-of-care treatment plus additional IT. Essentially, the IT consists of a sequential cisternal lavage with urokinase for 7 days starting from randomization, then with Ringer’s solution for another 4 to 14 days, and with nimodipine anytime between randomization and day 21 in case of verified or suspected CVS, administered via a stereotactically implanted catheter. Ringer’s solution will be used as a carrier solution for the other two investigational medicinal products (IMPs), urokinase and nimodipine, and as a third IMP. A graphic overview of the therapy protocol in group 2 is provided in Fig. 2 and a detailed dosing regimen in Table 3.

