**Fig. 2 Fig2:**
[figure not shown]
Therapy protocol in group 2

**Table 3 Tab3:** Dosing regimen of investigational medicinal products

Study medication	Pharmaceutical form and route of administration	Duration/regimen
Urokinase diluted in Ringer’s solution	Intrathecal use	Continuous cisternal lavage with 100 I.U. urokinase per ml Ringer’s solution at a rate of ~ 50 ml/h for 7 days following implantation of the catheter, i.e., from day 2 ± 2 until day 9 ± 2 after aSAH, or until the onset of cerebral vasospasm or DIND. Total daily dose: 120.000 I.U. Note: urokinase administration has to be stopped when nimodipine is given.
Nimodipine diluted in Ringer’s solution	Intrathecal use	Nimodipine is given on demand in case of vasospasm (i.e., delayed ischemic neurological deficit or mean flow velocities of any intracranial vessel > 120 cm/s on Doppler ultrasonography). In this case, nimodipine is administered as continuous cisternal lavage with 0.005 mg nimodipine per ml Ringer’s solution at a rate of ~ 50 ml/h. Nimodipine infusion is performed from the onset of vasospasm to the cessation of vasospasm, at least, however, for 24 h. If necessary, nimodipine can be administered as often as necessary or for extended periods during aSAH treatment (up to the entire aSAH treatment phase of this trial, i.e., up to 21 days). Total daily dose: 6 mg. Note: urokinase administration has to be stopped when nimodipine is given.
Ringer’s solution	Intrathecal use	Continuous cisternal lavage with Ringer’s solution at a rate of ~ 50 ml/h, starting from day 9 ± 2 (i.e., from the end of urokinase therapy) to day 18 ± 3 after aSAH; the exact stop date will be determined based on the investigator’s risk-benefit assessment for the individual patient. The criteria for this assessment are risk of catheter infection, macroscopic clearance of lavage fluid (i.e., no or minimal residual xanthochromia), and individual risk assessment for the development of vasospasm beyond day 15, considering patient neurological status, WFNS grade, sex, age, blood amount, and course of transcranial Doppler ultrasonographic measurements.

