Normal route of lavage (intracranial infusion via the cisternal STX-VCS catheter and outflow via the EVD) not possible, e.g., due to impaired outflow	Reversed flow direction (i.e., EVD in, cisternal catheter out).
Lavage therapy not feasible at the intended infusion rate	Lower infusion rate or small volume bolus lavage therapy.
Particular clinical circumstances (e.g., recurrent intracranial hemorrhage, persisting intraventricular/intracerebral/subarachnoid blood clots, refractory cerebral vasospasm, cerebral vasospasm lasting beyond day 21)	Recommencement and/or dose modifications of intrathecally administered urokinase or nimodipine.

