## Statistical methods

### Statistical methods for primary and secondary outcomes {20a}

The effects of the experimental vs. control intervention with respect to the primary endpoint will be estimated in the intention-to-treat (ITT) population by logistic regression. As an estimate of the effect size, the odds ratio will be given with a corresponding asymptotic two-sided 95% confidence interval. The two-sided test on the difference between the two trial arms at significance level 5% will be based on the corresponding asymptotic two-sided 95% confidence interval from the logistic regression model. Data should be collected regardless of the patient’s adherence to the protocol, especially on the clinical outcome, to obtain the best approximation to the full analysis set. Data should also be collected on other therapies received post-dropout. Specifically, full details of the type of additional (non-randomized) therapy given, including when and for how long it was used and at what dose, should be collected. In case of missing values for the primary endpoint, this will be handled by multiple imputation [20].

Secondary endpoints will be analyzed descriptively using regression models. Treatment effects will be calculated with two-sided 95% confidence intervals. Details will be specified in the statistical analysis plan (SAP) which will be finalized after the end of the recruitment period, but before the start of the final analysis.

Safety analyses will be performed in the safety set including all patients for whom one of the treatments was started. All safety parameters (e.g., adverse events, laboratory assessments) will be listed by the patient and displayed in summary tables. The adverse events (AEs) are displayed in summary tables by treatment as follows.

The total number of AEs; the minimum, maximum, and mean number of AEs per patient; the total number of follow-up days (number of days in the observation period); the number of AEs per FU-day; the number of patients who had at least one AE; and the number of patients who stopped treatment due to AE will be given.

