The incidence of AEs defined by the preferred term (PT) according to MedDRA will be calculated as the number of patients who experienced at least one AE with the respective PT in the percentage of the total number of patients in the safety population. In the incidence tables, the PTs will be grouped by system organ class (SOC) according to MedDRA. Additionally, the incidence of AEs defined by SOC will be calculated as the number of patients who experienced at least one AE in the respective SOC as a percentage of the total number of patients in the safety population.

Each table will be produced for the following AE sets: all AEs, AEs being at least severe, serious adverse events (SAEs), SAEs leading to death, AEs possibly related to IMP, AEs possibly related to IMP being at least severe (toxicity), SAEs possibly related to IMP, and SAEs possibly related to IMP leading to death. Incidences of AEs will be calculated with 95% confidence intervals.

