### Adverse event reporting and harms {22}

An adverse event (AE) is any untoward medical occurrence in a patient administered any dose of a pharmaceutical product which does not necessarily have a causal relationship with the use of the product. An AE can therefore be any unfavorable and unintended sign (including an abnormal laboratory finding), symptom, or disease temporally associated with the use of an IMP, whether or not related to the product.

In order to monitor the conditions of the patients from the time the patients receive the catheter implantation, the investigator is requested to report any untoward clinical event on the AE page of the CRF. Irrespective of any causal relationship, all AEs spontaneously reported by the patient or observed by the investigator will be documented in the case report form starting from randomization until the end of the study (month 6).

All AEs must be described by diagnosis or, if an underlying diagnosis is not known, by symptoms or medically significant laboratory or instrumental abnormalities. Symptoms, medically significant laboratory, or instrumental (e.g., electrocardiographic) abnormalities of a pre-existing disease are not considered an AE. Occurrences of new symptoms or laboratory or instrumental abnormalities, as well as worsening of pre-existing ones, are considered AEs. All AEs, no matter how intense, are to be followed up by the investigator in accordance with ICH-GCP until resolved or judged no longer clinically relevant or, in case of a chronic condition, until it is fully characterized.

For any AE, the following will be documented:
Characterization of the event (diagnosis; if not available, symptoms)Onset/end dateSeverity according to the common classification: (1) mild, (2) moderate, (3) severe, (4) life-threatening/disabling, and (5) deathRelationship to the IMP(s) (related/not related) or to study-specific procedures (such as stereotactic surgery or intrathecal lavage)Serious/non-seriousAction taken with IMP(s)Outcome

In this clinical trial, the following adverse events will be pre-specified (e.g., as a drop-down menu) for documentation in the CRF:
Delayed ischemic neurological deficit (DIND)DCIHydrocephalus requiring shunt implantationEndovascular interventions for the treatment of cerebral vasospasmComplications after aneurysm securingIntracerebral hemorrhageRe-SAHIntracerebral infection (meningitis and/or encephalitis)Episodes of critically increased ICP

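### The only time-adjusted adverse event summary spreads about 3 weeks of treatment over 6 months of follow-up, so this one descriptive rate can favour the arm with better survival (minor)

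*Protocol article*

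**What the plan says.** Section {20a} lists, by treatment, "the total number of follow-up days (number of days in the observation period); the number of AEs per FU-day". The same sentence also lists total AEs, AEs per patient (minimum, maximum, mean), the number of patients with at least one AE and the number who stopped treatment because of an AE. Incidences by preferred term and system organ class follow, as shares of the safety population with 95% confidence intervals. On scope the article says: "Each table will be produced for the following AE sets", and the sets include those possibly related to the investigational medicinal products (IMPs).

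Section {20a} does not define the observation period. The only AE window is in section {22}: all AEs "will be documented in the case report form starting from randomization until the end of the study (month 6").

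Section {11a} describes "sequential cisternal lavage with urokinase for 7 days starting from randomization, then with Ringer’s solution for another 4 to 14 days". The on-demand component has a window of its own in that section: "with nimodipine anytime between randomization and day 21 in case of verified or suspected CVS". Table 3 allows nimodipine "up to the entire aSAH treatment phase of this trial, i.e., up to 21 days". Table 4 permits treatment to be resumed or modified in particular circumstances, among them "cerebral vasospasm lasting beyond day 21". The article states no split of AEs into treatment phase and later follow-up.

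**The concern.** AEs per follow-up day is the only summary in the article that adjusts for how long patients were observed. A reader will turn to it when survival differs between arms, and that is the situation in which it is hardest to interpret. A patient followed to month 6 contributes mostly days without study drug; a patient who dies early contributes almost none of these. The denominator therefore depends on survival, which the treatment is meant to improve. If AEs are concentrated early, the arm with fewer early deaths shows a lower rate even when its daily rate during treatment is the same. Safety is a named secondary objective of this open-label trial of an invasive procedure, so a rate that mixes the two phases is a poor description of treatment-phase risk.

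**Working it through.** **The plan's own figures.** The article states no AE rate, so there is none to reproduce. The 50% and 15% used below come from section {14}. They do give its sample size: 27 per arm, 54 in total, power 0.8015, for a two-sided 5% chi-squared test without continuity correction.

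**Share of the denominator.** Lavage lasts 7 + 4 = 11 to 7 + 14 = 21 days. With randomization on day 2 and month 6 taken as day 182, a survivor contributes 180 days.
- 11/180 = 6.1% and 21/180 = 11.7%.
- If every IMP-related AE fell on a lavage day, the 6-month rate would be lower than the rate per lavage day by a factor of 180/21 = 8.6 to 180/11 = 16.4.

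This is a change of scale in the absolute rate. It does not by itself alter a comparison between arms.

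**Dependence on survival.** Assumptions, none of them in the article: a quarter, half or three quarters of the patients with mRS 4–6 (50% control, 15% experimental) die, all on day 12; 0.2 AEs per day up to day 21 in both arms; none later. With m the proportion who die:
- Follow-up days per patient: F = (1 − m)(182 − 2) + m(12 − 2) = 180(1 − m) + 10m
- Treatment-phase days per patient: T = 19(1 − m) + 10m
- AEs per follow-up day: 0.2 T/F

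| m control / experimental | F control / exp. | T control / exp. | Ratio per follow-up day (exp./control) | Ratio of mean AEs per patient (exp./control) |
|---|---|---|---|---|
| 12.5% / 3.75% | 158.75 / 173.63 | 17.88 / 18.66 | 0.95 | 1.04 |
| 25% / 7.5% | 137.50 / 167.25 | 16.75 / 18.33 | 0.90 | 1.09 |
| 37.5% / 11.25% | 116.25 / 160.88 | 15.63 / 17.99 | 0.83 | 1.15 |

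Middle row: 0.2 × 16.75/137.5 = 0.0244 and 0.2 × 18.325/167.25 = 0.0219, ratio 0.90. The true ratio of treatment-phase rates is 1.00 in every row. The per-patient mean departs from it in the other direction, because survivors have longer to accrue events.

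**Sensitivity.**
- Late AEs at 0.01 per day in both arms: 0.97, 0.93 and 0.88.
- Treatment-phase rate truly 20% higher in the experimental arm, no late AEs: 1.15, 1.08 and 1.00 per follow-up day. The mean number of AEs per patient shows 1.25, 1.31 and 1.38.
- Equal survival, a true 25% early excess and no late AEs: the ratio stays 1.25. With 30% mortality in both arms (deaths on day 14) and 4 versus 5 early AEs per patient, late AEs at 0.005 to 0.02 per day bring it to 1.22 to 1.16.

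**The case against.** The strongest defence is that this is one descriptive line among several. No ratio, test or confidence interval is planned for it. Total AEs and total follow-up days are both reported, so the rate is transparent, and numerator and denominator cover the same window. The per-patient counts and the incidence tables are not divided by follow-up days; in the scenario with a true 20% excess, mean AEs per patient shows it clearly. For the IMP-related sets the control arm receives no IMP, so there is no arm comparison to distort. All of this stands.

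Three stronger readings are tempting and not supported. One is that the safety analysis as a whole is diluted, or that a true excess of harm would go unseen; the other planned summaries rule this out. Another is that observation becomes sparse after intensive care. The article does not say so: the same AE documentation rule runs to month 6, the pre-specified events are actively evaluated at each visit, and the visit schedule is in a supplement not shown here. The third is that all risk ends by day 21: hydrocephalus requiring a shunt is a pre-specified AE, and Table 4 permits treatment later.

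It can also be said that phase-specific tables belong in the analysis plan, which is not shown and may already contain them. But the article itself names this measure and its denominator, and no summary it states gives the treatment-phase rate: the per-patient mean is itself moved by survival, to 1.04 to 1.15 when daily rates are equal.

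**Conclusion.** The point holds as a minor improvement. If AEs cluster in the treatment phase and early mortality differs between arms, AEs per follow-up day favours the arm with better survival, illustratively by 5% to 17% (ratios 0.95 to 0.83) when treatment-phase rates are equal. This rests on reading the observation period as randomization to month 6, which is inferred from section {22}, and on assumed mortality, time of death and AE rates. The 50% and 15% are proportions with mRS 4–6, which includes survivors, and the article gives no mortality by arm. With equal survival and no late AEs the comparison is unaffected.

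**What to change.** In section {20a}, or in the analysis plan before it is finalized:
- Define the observation period, and state the time origin from which day 21 is counted.
- Report AEs and AEs per patient-day separately for randomization to day 21 and for day 22 to month 6, each over its own patient-days. End the first phase earlier only at death or end of observation. Do not cut it at discharge, which could itself differ between arms.
- For the IMP-related sets, add a rate per day on treatment in the experimental arm.
- Keep the 6-month rate and the incidence tables, because some events and some permitted treatment fall after day 21.

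AE onset dates are already recorded under section {22}, so no new data item is needed for the split. The cost is a few extra table rows and one cut-off to fix in advance.

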### Objectives {7}

The primary objective of this trial is to assess whether sequential cisternal lavage with urokinase, nimodipine, and Ringer’s solution administered via a stereotactically implanted catheter into the basal cisterns (investigational treatment (IT)) improves neurological outcome in patients with aSAH compared to standard treatment, as measured by the Modified Rankin Scale (mRS).

Key secondary objectives include the assessment of the effect of the IT on rates of DCI and related complications, its effect on further clinical and surrogate endpoints, and its safety. Table 1 presents the secondary objectives and endpoints in detail.

**Table 1 Tab1:** Secondary objectives and endpoints

Secondary objectives	Secondary endpoints
To assess the effect of the IT on neuropsychological outcome	**Neuropsychological outcome** at 6 months following aSAH: - Cognitive performance (Montreal Cognitive Assessment) - Health-related quality of life (SF-36) - Fatigue, anxiety, and depressive symptoms (Frontal Systems Behavior Scale, Multidimensional Assessment of Fatigue, Hospital Anxiety and Depression Scale) - Post-traumatic stress disorder (Impact of Event Scale–R) Return-to-work parameters at 6 months
To assess the effect of the IT on DCI	Rate and severity of **DCI** according to the Vergouwen criteria
To assess the effect of the IT on **delayed ischemic neurological deficits (DIND)** after aSAH	Rate of delayed ischemic neurological deficit (DIND), defined as **clinical deterioration caused by delayed cerebral ischemia (i.e., a new focal neurological deficit or decline on the Glasgow Coma Scale of 1 point not attributable to other causes)** on days 3–21
To assess the effect of the IT on the development of post-hemorrhagic hydrocephalus	Rates of shunt-dependent **hydrocephalus** at 6 months following aSAH
To assess the effect of the IT on sonographic vasospasm	**Delta mean flow velocities** of both middle cerebral arteries—measured by transcranial Doppler ultrasonography on days 3–21
To assess the effect of the IT on the need for endovascular interventions for the treatment of cerebral vasospasm	Rate of **endovascular interventions** for the treatment of cerebral vasospasm
To assess the effect of the IT on the course of intensive care therapy	**Key parameters of intensive care medicine (Sequential Organ Failure Score)**
To assess the effect of the IT on **morphological brain damage**	**Morphological brain damage** at 6 months after aSAH as assessed by MRI

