	**Key markers of neuronal injury and systemic inflammation in patient blood**
	**Electroencephalographic patterns as measured by continuous EEG monitoring during intensive care period (exploratory endpoint)**
To assess the **safety of the IT**	**Safety of IT:** (serious) adverse events related to the IT

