The application of the IT requires a stereotactic neurosurgical intervention (STX-VCS) for catheter placement after aneurysm securing and randomization (on day 2 ± 2, usually day 2 or 3, ≤96 h after aSAH). Pre- and postoperative imaging (cCT) will be performed for the planning of surgery, verification of appropriate catheter position, and ruling out postoperative complications.

The STX-VCS procedure has been described in detail elsewhere [17, 19]. In the present clinical trial, the STX-VCS catheter is used for infusion of the IMPs, thus representing the inflow tract. A separate EVD—given to every patient with severe aSAH as a matter of clinical routine—represents the outflow tract. Figure 3 shows a schematic drawing of the setup during the administration of the IT.

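### All four relatedness-restricted adverse-event sets are limited to the IMP, so the stated safety endpoint, events related to the investigational treatment as a whole, has no summary table

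*Protocol article*

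**What the plan says.** Four parts of the protocol article bear on this.

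- **Endpoint.** The last row of Table 1 (Objectives {7}) gives the safety endpoint as "serious) adverse events related to the IT". Objectives {7} lists safety among the key secondary objectives, and the abstract makes it part of the primary objective.
- **What the IT is.** Objectives {7} describes a lavage "administered via a stereotactically implanted catheter into the basal cisterns (investigational treatment (IT". The intervention description adds: "The application of the IT requires a stereotactic neurosurgical intervention (STX-VCS) for catheter placement". The IMPs are the fluids only: "Ringer’s solution will be used as a carrier solution for the other two investigational medicinal products (IMPs), urokinase and nimodipine, and as a third IMP". Neither the operation nor the catheter is an IMP.
- **What is recorded.** Under Adverse event reporting and harms {22}, each event is documented with its relationship to the IMPs "or to study-specific procedures (such as stereotactic surgery or intrathecal lavage").
- **What is tabulated.** Section {20a} fixes the sets for which each table is produced. The first four are "all AEs, AEs being at least severe, serious adverse events (SAEs), SAEs leading to death". The rest are "AEs possibly related to IMP, AEs possibly related to IMP being at least severe (toxicity), SAEs possibly related to IMP", and finally the fatal serious events possibly related to the IMP. The tables are shown by treatment, and all safety parameters are also listed by patient.

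**The concern.** The endpoint, the data collection and the tables use three different scopes of relatedness. The endpoint refers to the IT. The case report form separates the IMP from study procedures. The tables use the IMP alone.

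This matters because the access route is the new element of the trial. The background section presents stereotactic ventriculocisternostomy as the answer to an unsolved access problem. A reader of the results will ask how many patients had an event that the investigators attributed to the operation or the lavage. If the stated list is followed, the related-event tables do not show this. A bleed along the catheter tract judged to be caused by the surgery and not by urokinase would not count as related in any summary table. The related-event tables would then describe the drugs, while the endpoint that they should report describes the whole treatment.

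**Working it through.** The plan gives no figure on this point, so the check is a count of the prescribed sets followed by a trace of where an event would appear.

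**Step 1: count the sets in section {20a}.**

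| Severity level | Regardless of relatedness | Related to IMP | Related to procedure | Related to IT (IMP or procedure) |
|---|---|---|---|---|
| All | yes | yes | no | no |
| At least severe | yes | yes | no | no |
| Serious | yes | yes | no | no |
| Serious and fatal | yes | yes | no | no |
| Sets | 4 | 4 | 0 | 0 |

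Total: 4 + 4 + 0 + 0 = 8, which is the whole list.

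**Step 2: trace an event by the attribution recorded under {22}.**

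| Recorded attribution | In all-cause sets | In a related set | Part of the Table 1 endpoint |
|---|---|---|---|
| IMP only | yes | yes | yes |
| IMP and procedure | yes | yes | yes |
| Stereotactic surgery only | yes | no | yes |
| Lavage procedure only | yes | no | yes |
| Neither | yes | no | no |

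The third and fourth rows are the gap: such events belong to the endpoint but are in no related set. The second row limits it, because an event attributed to both enters the IMP sets.

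**Step 3: does the document itself treat the procedure as distinct from the IMP?** It does in two places. Section {22} names surgery and lavage as study-specific procedures alongside the IMPs. Table 4 gives physical or mechanical effects of the fluid application their own row, apart from the pharmacological effects of urokinase and nimodipine. The term IMP in section {20a} therefore cannot simply be read as IT.

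**Step 4: how firm is each half of the gap?** For the surgery it is firm, since an operation is not an IMP under any definition in the document. For the lavage it is less certain. Ringer's solution is the lavage fluid and is itself an IMP, so an investigator could code a lavage harm as related to the IMP. Section {22} names lavage as a procedure, so the same harm could also be coded there. The documents do not settle which.

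**The case against.** Four objections deserve weight.

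**The all-cause tables already show these harms.** This is true. Surgical and lavage events are counted by arm, by preferred term and system organ class, with 95% confidence intervals. Intracerebral hemorrhage, intracerebral infection and critically raised intracranial pressure are pre-specified events that are actively sought at each visit. In an open-label randomized trial, the all-cause comparison is also the one least dependent on the investigator's causal judgement. It does not replace the endpoint in Table 1, however, which is defined by attribution. The pre-specified events can occur in both arms, and an external ventricular drain is routine in severe aSAH. With 54 patients randomized 1:1 (54 / 2 = 27 per arm), a few surgery-caused events may be hard to tell from that background.

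**The listings show relatedness.** They can, since relationship is documented for each event. A listing is not a summary, though, and gives no incidence.

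**The statistical analysis plan may add sets.** Section {20a} defers details of the secondary endpoints to that plan and does not call the list exhaustive. This stands in part. Even so, the article does not leave the matter open: it states which sets each table will cover, and that list does not match its own endpoint.

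**Some lavage harms may be coded to the IMP.** This stands, and for lavage the gap depends on coding.

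A reader might also infer a denominator error, because incidence is described "in the percentage of the total number of patients in the safety population" rather than of the arm. The documents do not support that. The tables are displayed by treatment, and section {20c} assigns safety patients to the arm of the treatment received. Read together, the denominator is the safety population of the arm.

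**Conclusion.** The point holds in a limited form. Of the eight prescribed AE sets, four are regardless of relatedness, four are restricted to the IMP, and none covers the procedure or the IT as a whole. The safety endpoint as worded therefore has no summary table, although the data for it are collected.

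A reader might go further and infer that the tables cover only IMP-related events, or that the plan hides or understates surgical harm. Neither follows. Half of the sets ignore relatedness and count every such event by arm, and the patient listings can show the recorded attribution. What is absent is one summary, the attributed one, and that is the one which the endpoint names.

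The conclusion rests on two assumptions: that the stated list is followed as written, and that at least some events are attributed to a procedure and not also to an IMP. How many that would be cannot be derived from the documents. The primary efficacy analysis is not affected.

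**What to change.** In section {20a}, or in the statistical analysis plan before it is finalized, add two families of AE sets:

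1. related to a study procedure (stereotactic surgery, lavage);
2. related to the IT, meaning related to an IMP or to a study procedure.

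Produce each for all, at least severe, serious and fatal events, matching the four levels already used for the IMP. That makes 2 × 4 = 8 further sets, for 16 in total. Name the second family as the summary that reports the safety endpoint of Table 1. Because it combines both attributions, it also removes the dependence on whether a lavage harm was coded to the Ringer's solution or to the procedure.

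Define the sets by the related/not-related coding that section {22} records, since the present list speaks of possibly related events. The surgery and lavage belong to group 2 only, so the new tables describe that arm; the all-cause tables remain the comparison between arms and should stay.

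The cost is a few extra tables from data already collected, with no change to the case report form, the sample size or the conduct of the trial.
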